## Abstract

**Background:**

Acute pancreatitis is the most common complication of diagnostic and therapeutic endoscopic retrograde cholangiopancreatography (ERCP). In spite of continuing research, no pharmacologic agent capable of effectively reducing the incidence of ERCP-induced pancreatitis has found its way into clinical practise. A number of experimental studies suggest that intrapancreatic calcium concentrations play an important role in the initiation of intracellular protease activation, an initiating step in the course of acute pancreatitis. Magnesium can act as a calcium-antagonist and counteracts effects in calcium signalling. It can thereby attenuate the intracellular activation of proteolytic digestive enzymes in the pancreas and reduces the severity of experimental pancreatitis when administered either intravenously or as a food supplement.

**Methods:**

We designed a randomized, double-blind, placebo-controlled phase III study to test whether the administration of intravenous magnesium sulphate before and after ERCP reduces the incidence and the severity of post-ERCP pancreatitis. A total of 502 adult patients with a medical indication for ERCP are to be randomized to receive either 4930 mg magnesium sulphate (= 20 mmol magnesium) or placebo 60 min before and 6 hours after ERCP. The incidence of clinical post-ERCP pancreatitis, hyperlipasemia, pain levels, use of analgetics and length of hospital stay will be evaluated.

**Conclusions:**

If magnesium sulphate is found to be effective in preventing post-ERCP pancreatitis, this inexpensive agent with limited adverse effects could be used as a routine pharmacological prophylaxis.

**Trial registration:**

Current Controlled Trials
ISRCTN46556454

## Background

Endoscopic retrograde cholangiopancreatography (ERCP) is a common procedure employed to treat disorders of the biliary tract or the pancreas. In Germany around 124.000 ERCP’s (OPS 1–64, diagnostic ERC, ERP or ERCP) are performed annually (German federal statistics bureau for 2009). The most common complication of ERCP is procedure-related acute pancreatitis, which occurs in 2 to 9% of patients in unselected prospective studies
[1]. When an average rate of 5% is assumed, 6200 pancreatitis cases in Germany would be triggered by prior ERCP and thus 12% of the total 53.338 in-hospital pancreatitis cases in the country (German federal statistics bureau for 2009). The severity of post-ERCP pancreatitis can range from mild disease with full recovery to critical illness with pancreatic necrosis, multiple organ failure, prolonged hospitalization and even death. Of all cases of post-ERCP pancreatitis approximately 10% are severe and up to 1% take a fatal course
[2]. The national in-hospital mortality for acute pancreatitis is 2.9% in Germany and ERCP-induced pancreatitis would thus account for at least 180 deaths.

Efforts to reduce the incidence and severity of post-ERCP pancreatitis have been made for more than thirty years. So far, the search for a pharmacologic agent that would be effective and broadly introduced into clinical routine has been unsuccessful. Some of the pharmacologic agents that have been tested for the prophylactic administration before and during ERCP are gabexate mesilate
[3-5], octreotide
[6], somatostatin
[7,8], allopurinol
[9,10], corticosteroids
[11], NSAIDs
[12], heparin
[13] and interleukin-10
[14]. The most promising study suggests the routine use of diclofenac suppositories but has demonstrated its effectiveness only in very high risk patients
[15].

One critical event for the development of acute pancreatitis is premature intracellular zymogen activation leading to pancreatic autodigestion
[16]. Extra- as well as intracellular calcium concentrations have been shown to play an important role in the initiation of intracellular pancreatic protease activation and the onset of pancreatitis
[17,18]. Moreover, pathological sustained calcium signals have been shown to strongly reduce bicarbonate secretion from pancreatic duct cells
[19,20], which may be relevant for the initiation of post-ERCP pancreatitis. Magnesium, a critical cofactor for multiple enzymatic reactions, acts as a natural calcium-antagonist in the exocrine pancreas and can counteract the effect of pathological calcium signals on premature intracellular protease activation and cell necrosis
[21]. In animal models of acute pancreatitis Mg^2+^ administration not only reduced the intrapancreatic activation of digestive enzymes but also ameliorated the local and systemic damage associated with the disease
[22].

Based on these *in vitro* and animal experiments we designed a multicentre, randomized placebo-controlled phase III trial to study the efficacy of magnesium-sulphate in preventing the onset and reducing the severity of acute post-ERCP pancreatitis. The “Magnesium sulphate in the prevention of post-ERCP pancreatitis study” (MagPEP) aims to provide robust data on the effectiveness of peri-interventional intravenous magnesium sulphate administration in reducing the incidence and severity of post-ERCP pancreatitis.

## Methods

### Trial organisation and coordination

MagPEP is designed and coordinated by the Department of Medicine A at University Medicine Greifswald, which is responsible for overall trial management, regulatory affairs, statistical planning and analysis, trial registration and reporting as well as quality assurance. Monitoring is carried out by the Clinical Trial Coordination Centre at Greifswald University Medicine. MagPEP will be conducted as a multicentre trial in Germany and Hungary, including (as of November 2012) ten academic medical centres. The trial is sponsored by the University Hospital Greifswald, represented by the CEO, and the Deutsche Forschungsgemeinschaft (DFG), neither of which is involved in the database management or has access to the randomisation code.

### Investigators

Patients will be recruited by the respective centres who will commit their participation in a contractual agreement with the sponsor. All investigators will be experienced gastroenterologists and endoscopists. Centres participating in the trial will have a volume load of > 400 ERCP per annum.

### Data safety and monitoring board

An independent Data Safety and Monitoring Board (DSMB) consisting of three independent experts will evaluate the clinical research data on an ongoing basis to assure patient safety and study integrity. The board will monitor the trial data, particularly the safety data, and give their advice based on the periodical reviews. Responsibilities are recorded in a DSMB chart.

### Medication supply

Study medication and placebo will be prepared and provided by the university pharmacy in Greifswald which is ICH-GCP approved and audited by the state regulatory authorities.

### On-site monitoring

On-site monitoring of the centres will be performed according to good clinical practice (ICH-GCP) guidelines. In person visits carried out according to the SOPs of the Clinical Trial Coordination Centre at Greifswald University Medicine, clinical monitors will review all entries into CRFs on the basis of source documents (minimum of 30% source data verification) and perform the data management.

### Ethical considerations

The final protocol has been approved by the ethics committee at the Medical Faculty of the Ernst-Moritz-Arndt-University Greifswald on August 27th 2010 (Registration number: FFV 04/10) and adheres to the declaration of Helsinki, the Medical Association’s professional code of conduct, the principles of ICH-GCP guidelines and the Federal Data Protection Act. The trial will also be performed in keeping with local legal and regulatory requirements. The medical secrecy and the Federal Data Protection Act will be followed. Consent to the master ethics committee approval has been obtained from the local ethics committees of all participating centres.

Before enrolment, each patient will be given a detailed briefing on the nature, scope and possible consequences of the trial by a physician and then give written informed consent. No measures required specifically for the clinical trial will be taken without valid consent having been obtained from the patient.

### Study objectives

The primary objective of this study is to determine whether intravenous magnesium sulphate administrated before and after the intervention can reduce the incidence and severity of post-ERCP pancreatitis by 50% i.e. (from 7.4%, the incidence in Greifswald, Germany, in 2004–2005, to 3.7%). Secondary objectives include the evaluation of (1) the severity of post-ERCP pancreatitis, the (2) administration of analgesics, the (3) duration of the hospital stay, the (4) lipase levels measured 6 and 24 hours after ERCP and the (5) 30-days mortality as determined in a telephone interview 30 days after ERCP.

### Definitions

Acute post-ERCP pancreatitis is defined as the presence of typical abdominal pain at 24 hours post ERCP in combination with an elevation in serum lipase level to at least three times the normal upper limit. Severity of pancreatitis is classified according to the 1991 Consensus Guidelines published by Cotton et al.
[23]: mild pancreatitis leading to a prolongation of hospitalization by up to three days, moderate pancreatitis requiring four to ten days of hospitalization and severe pancreatitis involving hospitalization for more than ten days and evidence of necrotizing pancreatitis and/or infected necrosis or pseudocyst (fluid collection) development.

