### Patients

In all of the participating academic gastroenterology departments in Germany and Hungary, all adult (≥ 18 years of age) patients with a clinical indication for ERCP will be screened for eligibility for the trial. Exclusion criteria are listed in Table 
1. Only patients who have not previously undergone an ERCP will be included in the study.

**Table 1 T1:** Exclusion ciriteria

•	Previous ERCP
•	Known allergy or intolerance to one of the compounds used in the study
•	Participation in another interventional trial during the previous four weeks
•	Pregnancy and breast feeding
•	current acute pancreatitis
•	Renal insufficiency ≥ stage 4 (K/DOQI), i.e. MDRD-GFR < 30 ml/min/1,73 m^2^)
•	Hyperthyroidism
•	Symptomatic bradycardia <35 bpm
•	Atrioventricular block > 1° or other cardial conduction defects
•	Myasthenia gravis
•	Liver cirrhosis Child C
•	Overt coagulopathy
•	Kidney stone diathesis (calcium-magnesium-ammonium-phosphate stones)
•	Mental impairment, addiction or other disorders leading to the patients inability to understand the scope and possible consequences of a participation in a clinical trial
•	Magnesium medication within 14 days before the procedure
•	Inability to give informed consent

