### Treatment scheme

All randomized patients receive an intravenous infusion 60 min before the start and 6 hours after the end of ERCP. To prevent adverse reactions to magnesium, which are seen more frequently if the substance is injected rapidly, the first infusion is given over 60 min, the second infusion is given over 2 hours. In the magnesium arm 500 ml NaCl 0,9% containing 10 ml magnesium sulphate 50% (= 4930 mg magnesiumsulphate-heptahydrate; magnesium content: 486,1 mg = 20 mmol = 40 mval) will be administered. In the placebo arm 500 ml NaCl 0,9% + 10 ml NaCl 0,9% will be given in the same manner. Test substance vials are labelled with protocol and randomization number only giving no indication as to their content.

The ERCP intervention will be carried out according to the established clinical practice at the respective centre and in no way differently as compared to patients not participating in the study. After completion of the ERCP, the endoscopist is going to fill out a questionnaire on the details of the procedure, giving information e.g. on the final endoscopic diagnosis, the number of pancreatic duct injections, cannulation difficulties, the duration of the procedure, among other procedural details.

Six and 24 hours after ERCP patients are asked to assess their pain level using a visual analogue scale and the pain medication required and used is recorded. In addition, a clinical examination of the abdomen is performed and a blood sample is taken. To ensure blinding the clinician in charge of the patient is not allowed to order any tests on blood magnesium concentration unless in an emergency, which will lead to the exclusion of the patient. If post-ERCP pancreatitis develops blood samples, clinical examination, pain assessment and documentation of pain medication is continued until the day of discharge from the hospital.

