### Safety considerations

The assessment of safety will be based mainly on the frequency of adverse events (AEs) and on the number of laboratory values falling outside of pre-determined ranges. AEs will be summarized by presenting the number and percentage of patients having any AEs or serious adverse events (SAEs) and for each individual AE. Furthermore, the most common AEs (those occurring in at least 10% of the respective group) will be determined. Any other information collected (e.g. severity or relatedness to study drug) will be listed as appropriate. Laboratory data will be summarized by presenting shift tables using normal ranges (baseline to most extreme post-baseline value) and by presenting summary statistics of raw data and changes from baseline values (means, medians, standard deviations, ranges). The analysis of safety and tolerability will be based on all patients entered into treatment who received at least one application of the study medication. All proportions will be given along with exact Pearson-Clopper 95% confidence bounds.

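### The primary end-point is an absolute state after ERCP with no reference to pain or lipase beforehand, so some counted events would not be reliably attributable to the procedure

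*Protocol article*

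**What the plan says.** The Definitions section of the protocol article gives the event two parts. The first is pain: "Acute post-ERCP pancreatitis is defined as the presence of typical abdominal pain at 24 hours post ERCP". The second is lipase: "in combination with an elevation in serum lipase level to at least three times the normal upper limit". Presence of pain is enough, and the lipase threshold is absolute.

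Other sections bear on how this works in practice:

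- **Background** describes ERCP as "a common procedure employed to treat disorders of the biliary tract or the pancreas", so the enrolled patients have such a disorder, known or suspected.
- **Patients** admits adults with a clinical indication for a first ERCP. The only entry in Table 1 that addresses a pancreatic condition present beforehand is "current acute pancreatitis", and no criteria are given for it.
- **Treatment scheme** sets the pain scores: "Six and 24 hours after ERCP patients are asked to assess their pain level using a visual analogue scale". The text mentions no score before ERCP.
- **Study objectives** names "lipase levels measured 6 and 24 hours after ERCP" as a secondary objective.
- **Safety considerations** summarises laboratory data "by presenting summary statistics of raw data and changes from baseline values". Some baseline laboratory data therefore exist, but lipase is not named and no link to the primary end-point is made.

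**The concern.** The trial asks whether magnesium prevents pancreatitis caused by ERCP. An end-point that ignores the starting state can be completed by the disease that led to the ERCP. Two hypothetical patients show how:

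- One has biliary or chronic pancreatic pain and a lipase of 2.8 times the upper limit before ERCP. The next day the pain is unchanged and the lipase is 3.1 times the limit.
- Another has no pain before ERCP but a lipase already above three times the limit. Abdominal pain judged typical is present at 24 hours.

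Both count as primary events under the written definition, and in both the contribution of ERCP is uncertain. If magnesium acts on pancreatitis triggered by the procedure, events of this kind respond less to it. The observed relative reduction then understates the effect on the condition of interest. That matters in a trial whose stated aim is a 50% reduction.

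**Working it through.** **Inputs from the protocol article**

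- Control rate 7.4%, target 3.7% (Study objectives; Sample size considerations assumes 7.4% for the primary end-point).
- 251 patients per arm (Sample size considerations).

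**Assumed input.** Let *f* be the part of the control rate that is not preventable, equal in both arms. The documents give no value, so a range is shown.

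**Step 1: the plan's own effect.** 3.7 / 7.4 = 0.50, a 50% relative reduction.

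**Step 2: such events lie within the 7.4%.** This keeps the plan's control rate. The drug halves only the preventable part:

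RR = [(7.4 − f)/2 + f] / 7.4

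- f = 1 point: (3.2 + 1.0)/7.4 = 4.2/7.4 = 0.57
- f = 2 points: (2.7 + 2.0)/7.4 = 4.7/7.4 = 0.64

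For scale, 7.4% of 251 is 18.6 control events, and 1 point is 2.5 of them. As shares of all control events, 1 point is 1/7.4 = 13.5% and 2 points are 2/7.4 = 27%.

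**Step 3: such events come on top of 7.4% and 3.7%.** This departs from the plan's stated control rate.

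RR = (3.7 + f)/(7.4 + f)

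- f = 1: 4.7/8.4 = 0.56
- f = 2: 5.7/9.4 = 0.61
- f = 3: 6.7/10.4 = 0.64

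The two placements agree closely for the same *f*, so the dilution does not depend on how the historical 7.4% was counted.

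**Step 4: effect on the numbers needed.** The control rate is held at 7.4%, and a share *s* of control events is taken as not preventable, so p2 = 7.4% × [s + (1 − s)/2]. The usual two-proportion formula (two-sided 5%, 80% power, before drop-out) is

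n per arm = [1.96·√(2p̄(1−p̄)) + 0.842·√(p1(1−p1) + p2(1−p2))]² / (p1 − p2)², with p̄ = (p1 + p2)/2.

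| Share *s* | Treated rate | RR | n per arm for 80% power | Power at 251 per arm |
|---|---|---|---|---|
| 0 | 3.70% | 0.50 | 600 | 44% |
| 10% | 4.07% | 0.55 | 765 | 36% |
| 20% | 4.44% | 0.60 | 997 | 29% |
| 30% | 4.81% | 0.65 | 1341 | 23% |

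The first row does not reproduce the stated 251 per arm. That is a separate matter and does not bear on this point. What counts here is the change down the table: a 10% share raises the number needed by 765/600 − 1 = 27.5%.

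**The case against.** **The event is more specific than it may look.** Pain must be typical, and the condition is named as acute and post-ERCP. This stands in part. It helps to screen out ordinary discomfort after the procedure, but not continuing pain from biliary or pancreatic disease. The lipase wording could also be read as a rise to the threshold, but no comparison with an earlier value is stated, and the ambiguity itself needs resolving.

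**The exclusion of current acute pancreatitis removes the worst cases.** This largely stands. A patient with both typical pain and lipase at or above the threshold beforehand meets the protocol's own two criteria and should mostly be kept out. What remains are mixed cases. A reader might infer that these are events no prophylaxis could prevent, or that were already complete before the first infusion. The documents do not support that: in both examples above, one component first appears after ERCP. The supportable statement is that attribution to ERCP is unreliable.

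**The article is condensed.** A reader might infer that no pain score is taken before ERCP, or that a baseline lipase is already available. Neither can be confirmed. The patient pathway is in Figure 1, which is not shown; the full protocol may hold a baseline assessment; and Safety considerations does not name lipase. This stands, but it does not rescue the definition, which as written would not use a baseline value even if one existed.

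**The size has no source.** This stands. Two points within 7.4% would mean that 27% of control events were not preventable, and nothing in the documents supports that share. The figures show the direction and mechanism of dilution, not its actual extent.

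**Conclusion.** The point holds as a weakness in a stated rule. The primary end-point records a state after ERCP without reference to the state before it, and the eligibility criteria leave room for existing pain or a raised lipase to supply one of its two components.

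The consequence is dilution, not bias towards a positive result. Under double-blind 1:1 randomisation both arms are expected to carry such events equally, so a reader should not infer a raised risk of a false-positive finding.

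The illustrative relative risks of 0.57 and 0.64 rest on three assumptions: that 1 or 2 points of the 7.4% are not preventable, that this part is equal in both arms, and that the drug halves everything else. If mixed cases are partly preventable, or the exclusion works well, the dilution is smaller. The change is worth making because it is cheap and the end-point is primary; the documents do not show that the loss is large.

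**What to change.** 1. Reword the definition so that the abdominal pain must be new, or worse than a pain score recorded before the first infusion, and state in advance how much worse counts. If the full protocol has no such score, add one visual analogue score at that time.
2. State how a lipase already raised before ERCP is handled, using a baseline lipase value. Asking only for a value higher than before is not enough: a move from 2.8 to 3.1 times the limit would pass, and only the pain condition would remove that case.
3. Report the present absolute definition as a sensitivity analysis.

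**Cost.** One extra pain score, a baseline lipase if the baseline bloods do not already include it, and a reworded definition. Somewhat fewer events will be counted. A few genuine cases may also be lost, namely patients whose earlier pain was as severe as the pain of a true post-ERCP pancreatitis; the sensitivity analysis will show whether this matters.

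### As worded, the severity scale leaves stays over ten days without a local complication ungraded and places necrosis with a shorter stay below severe

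*Protocol article*

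**What the plan says.** The Definitions section of the protocol article names its source, "Severity of pancreatitis is classified according to the 1991 Consensus Guidelines", and then writes out three classes in one sentence:

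- Mild: "mild pancreatitis leading to a prolongation of hospitalization by up to three days".
- Moderate: "moderate pancreatitis requiring four to ten days of hospitalization".
- Severe: "severe pancreatitis involving hospitalization for more than ten days and evidence of necrotizing pancreatitis and/or infected necrosis or pseudocyst (fluid collection) development".

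The Study objectives section uses the scale: "Secondary objectives include the evaluation of (1) the severity of post-ERCP pancreatitis". Severity also appears in the primary objective, which asks whether magnesium "can reduce the incidence and severity of post-ERCP pancreatitis by 50" per cent, although the figures given there are incidences. The Background describes the critical end of the disease as "pancreatic necrosis, multiple organ failure, prolonged hospitalization and even death".

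The article does not say how to grade a long stay without a local complication or a local complication with a short stay. Nor does it say what to do when a patient meets two classes.

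**The concern.** An ordinal outcome scale should give every case exactly one grade, and worse disease should not receive a lower grade. The severe class joins its two conditions with a plain conjunction. The same clause uses and/or and or between the complications, so it marks alternatives elsewhere. Read that way, the scale has a hole above ten days. A local complication also has no influence on the grade until the stay passes ten days. That sits badly with the Background, which puts necrosis at the critical end of the range.

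The change of unit between mild and the other two classes is a second, weaker problem. Ten centres were taking part as of November 2012, and they could resolve either point differently. At stake is the comparison under secondary objective (1), which rests on very few severe cases.

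**Working it through.** The plan gives no figure to reproduce here, so the check applies the three criteria exactly as worded. Below, *local complication* means necrosis, infected necrosis or pseudocyst.

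**Reading A: the same day count for all three classes.**

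| Days | No local complication | Local complication |
|---|---|---|
| 1 to 3 | mild | mild |
| 4 to 10 | moderate | moderate |
| 11 or more | no class | severe |

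The classes do not overlap. One cell is empty, and in the first two rows a local complication makes no difference to the grade.

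**Reading B: mild counts extra days; moderate and severe count total days.** The planned stays are illustrative.

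| Planned + extra = total days | Local complication | Classes met |
|---|---|---|
| 2 + 10 = 12 | no | none |
| 1 + 3 = 4 | no | mild and moderate |
| 2 + 3 = 5 | no | mild and moderate |
| 2 + 4 = 6 | yes | moderate |
| 9 + 2 = 11 | yes | mild and severe |

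The gap and the downgrading remain, and overlaps now appear. So the gap and the downgrading come from the conjunction and hold under both readings. The overlap comes from the mixed units and holds only under Reading B.

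**How many severe cases are expected.** Inputs: 251 patients per arm (Sample size considerations); incidence of 7.4% on placebo and 3.7% on magnesium (Study objectives); approximately 10% of cases severe and up to 1% fatal (Background).

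- Placebo: 251 × 0.074 = 18.6 cases.
- Magnesium: 251 × 0.037 = 9.3 cases.
- Total: 18.6 + 9.3 = 27.9 cases.
- Severe: 0.10 × 27.9 = 2.8, or about 1.9 on placebo and 0.9 on magnesium.
- Fatal: at most 0.01 × 27.9 = 0.3.

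If magnesium had no effect, the total would be 502 × 0.074 = 37.1 cases, of which 3.7 severe. Either way the trial expects about three or four severe cases.

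**What cannot be computed.** The article gives no share of cases with a stay over ten days and no local complication, nor of cases with a local complication and a shorter stay. The number of misplaced patients therefore has no estimate.

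**The case against.** The strongest reply is that the operative rule is the cited guideline and the sentence is only a condensed paraphrase, so graders may use a complete scale. Neither the guideline nor the full protocol is at hand, so this cannot be excluded. It does not repair the article, which spells out its own criteria; a reader applying them would meet the gap. It does mean that the remedy must start from the guideline.

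Several stronger readings are tempting, and the objections to them stand:

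- *The classes overlap.* A reader might infer this as fact. The cut-points run on without a break (up to three, four to ten, more than ten), which suits a single day count, and under a single count there is no overlap. It is an ambiguity.
- *Early deaths would be hidden as mild or moderate.* The wording allows it, but at most about 0.3 deaths from pancreatitis are expected. Thirty-day mortality is separately secondary objective (5), so a death is not lost if its severity label is wrong.
- *Misgrading would overturn the severity result.* That depends on such patients occurring, and their number is not estimable. With about three severe cases, a comparison of severe cases alone says little under any definition.
- *The primary endpoint is compromised.* Pancreatitis is defined by pain and lipase, and the sample size uses incidence only. The mention of severity in the primary objective adds no weight to this point.

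**Conclusion.** The definition is wrong as written; this is not a detail left to a fuller document. On its literal wording it leaves one kind of case ungraded and lets a local complication with a stay of ten days or less fall below severe, whichever day count is used. The mixed day count is an ambiguity that produces overlap only if total days are meant.

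The consequence is confined to secondary objective (1). With about 3 severe cases expected in 502 patients, a few ungraded or downgraded patients could matter. That figure assumes the article's incidences and its Background share of 10% severe, a share not stated to have been obtained under this trial's wording. No claim about the size or direction of any bias can be supported. The point deserves correction because the repair is specific and nearly free.

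**What to change.** Reconcile the severity sentence with the guideline it cites, so that every case receives exactly one grade:

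1. Use one day count for all three classes, namely days attributable to pancreatitis after ERCP, and state it.
2. Make severe reachable by more than ten days **or** by necrosis, infected necrosis or pseudocyst, whatever the stay.
3. Assign the highest class met.
4. Confirm that the case report form records local complications. The article lists blood samples, clinical examination, pain and pain medication until discharge for patients who develop pancreatitis, but does not mention recording necrosis or pseudocyst.

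If the guideline proves to be worded differently, state any departure from it. The cost is a change of definition wording and possibly one form field. The change does not affect the incidence endpoint or the sample size.
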